### Control (TAU) group

Participants in the TAU group receive weekly messages and will be asked to answer short screening questionnaires on their depressive symptoms each week. Similar to the intervention group, alert messages and information on mental health care will be shown if the participants present with severe depressive symptoms or suicidal thoughts. They are also allowed to receive treatment as usual, including inpatient and outpatient medical care.

### Outcomes

The schedule of assessments is summarized in Table 2. The co-primary outcomes are measured in the baseline, with 12- and 24-week follow-up online surveys. Participants who have not completed follow-up surveys will receive weekly reminders to complete their surveys.

**Table 2 Tab2:** Schedule of enrolment, interventions, and assessments

		Enrolment	Allocation	Post-allocation	
TIMEPOINT		T0	0	12 weeks follow-up (T1)	24 weeks follow-up (T2)
**ENROLMENT:**					
Eligibility screen		X			
Informed consent		X			
Allocation			X		
**INTERVENTIONS:**					
Intervention group					
Control group					
**ASSESSMENTS:**	**Aim**				
**Co-primary outcomes**					
EPDS	Maternal depressive symptoms	X		X	X
CTS-1	Psychological aggression toward children	X		X	X
**Secondary outcomes**					
**Maternal**					
PHQ-9	Depresssive symptoms	X		X	X
PSI-SF	Parent stress	X		X	X
MIBS-J	Mother-to-infant bonding	X		X	X
EQ-5D-5L	Quality of life	X		X	X
Use of inpatient and outpatient medical care in the past 3 months	Medical cost	X		X	X
**Paediatric**					
Height, body weight	Physical development	X		X	X
Type of nutrition (breast milk, formula, both, baby food)	Nutritional status	X		X	X
Attendance of well-baby visits at 1, 3, 6–7, 9–10 months)	Health check-up status	X		X	X
Immunization record (Hib, pneumococcus, DPT-IPV, rotavirus, BCG)	Immunization status	X		X	X
Use of inpatient and outpatient medical care for injuries, foreign body ingestion, burn, and drowning in the 3 months	Medical cost for injuries	X		X	X
**Implementation**					
Implementation outcome scale for Digital Mental Health (IDMH) for users	Acceptability, appropriateness, feasibility, overall satisfaction, and harms			X	

*EPDS* Edinburgh Postnatal Depression Scale, *CTS-1* Conflict Tactics Scale, *PHQ-9* Patient Heatlh Questionnaire-9, *PSI-SF* Parent stress index-short form Japanese version, *MIBS-J* Mother-to-Infant Bonding Scale Japanese version, *EQ-5D-5L* EuroQol-5 dimension-5 level

### Co-primary outcomes

The co-primary outcomes of the study are the depressive symptoms at 24 weeks after initiation of the program and aggression toward their children at 24 weeks after the initiation of the program. We have set two co-primary outcomes, as both maternal and child outcomes were considered equally important.

### Depressive symptoms

The depressive symptoms of participants will be assessed with the EPDS score measured in online surveys. The EPDS is a reliable and valid screening tool that is widely used in perinatal medical and healthcare settings in Japan [50, 53]. Participants are asked to self-report their depressive symptoms on a scale of 0 to 3 for 10 items (total score range being 0–30).

### Psychological aggression toward children

The study uses psychological aggression toward children as outcomes of abusive behaviours toward children. Psychological aggression toward children will be measured by the psychological aggression item of the Conflict Tactic Scale I (CTS-1), a Japanese version developed by Kitamura, et al. [54]. The CTS-1 is a commonly used self-report measure for abusive behaviours toward children that has been tested for its validity [55, 56]. The participants will be asked to answer the seven items on psychological aggression, on a scale of 0 to 6, with a higher score indicating more severe psychological aggression.

### Secondary outcomes

#### Maternal depressive symptoms

Depressive symptoms of participants will be evaluated by the Patient Health Questionnaire-9 (PHQ-9). The PHQ-9 is a brief and straightforward self-report instrument to screen and measure the severity of depressive symptoms. The PHQ-9 correlates with the Diagnostic and Statistical Manual of Mental Disorders, Fourth Edition (DSM-IV) criteria for the major depressive disorder [57, 58].

#### Parental stress

Parental stress will be assessed by the Japanese version of the Parental stress index-short form (PSI-SF). The PSI-SF is a self-report screening tool that consists of 19 questions— 9 questions for child characteristics, and 10 questions for parent characteristics on a 5-point Likert scale. A previous study indicates acceptable reliability and internal validity [59].

#### Bonding relationship

Mother-to-infant bonding relationship will be measured by the Mother-to-Infant Bonding Scale Japanese version (MIBS-J). The MIBS-J is a self-report questionnaire that consists of 10 questions to assess a mother’s feelings toward her child on a 4-point Likert scale. The MIBS-J is widely used in health care settings in Japan, and has acceptable reliability and validity [60].

#### Physical assault

Maltreatment measures including both minor and major physical assault are measured with 9 physical assault items of CTS-1 [54–56], as mentioned in the psychological aggression section. The participants will be asked to answer the nine items on physical assault on a scale of 0 to 6, with a higher score indicating more severe physical assault.

#### Quality of life

The quality of life is measured with the EuroQol-5 dimension-5 level (EQ-5D-5L). The EQ-5D-5L is an instrument consisting of five items with five levels to evaluate the health status of the population. The five dimensions include mobility, self-care, usual activities, pain/discomfort, and anxiety/depression. It is widely used and has acceptable reliability and validity according to previous studies [61, 62].

#### Healthcare use for mothers

Healthcare use for mothers will be evaluated by questions on the inpatient and outpatient healthcare use for psychiatric problems faced by the participants (the number of days for outpatient visits and hospitalization), or home visitation by public health nurses in the past 3 months during the 12–24 week surveys.

#### Paediatric physical development

The physical development of children will be assessed by standard deviation scores for body weight and height based on the recent records of children’s body weight and height during the 12-week and 24-week follow-up surveys.

#### Health check-up attendance

Health check-up attendance will be evaluated by asking questions about whether children have attended well-baby check-ups at 3, 6, and 9 months (if applicable) during the 12-week and 24-week follow-up surveys.

#### Immunization status

Immunization status will be evaluated by asking questions about whether children have completed immunization for Hemophilus influenzae type b, *Streptococcus pneumoniae*, diphtheria, tetanus, pertussis, and polio (DPT-IPV) during the 12–24 week follow-up surveys.

#### Healthcare use for children

The healthcare use of children will be evaluated by asking questions about the inpatient and outpatient healthcare use for injuries, fractures, burns, foreign body ingestions, skin problems, or nutrition problems in the past 3 months. Healthcare questions will be administered during the 12–24 weeks of follow-up surveys.

#### Implementation outcomes

Implementation outcomes will be measured by the Implementation Outcome Scale for Digital Mental Health (iOSDMH) and the System Usability Scale (SUS). The iOSDMH has been developed to cover the key concepts of implementation in digital mental health, including acceptability, appropriateness, and feasibility, based on a previous systematic review [63]. The iOSDMH evaluates these implementation concepts among different levels of stakeholders involved in the intervention process, including users, providers, and managers. Participants will be asked to answer the questionnaires consisting of 19 items from the iOSDMH for users on acceptability, appropriateness, feasibility, and harms, as well as 10 items on usability at the 12-week follow-up survey. Medical providers will be asked to answer the iOSDMH questionnaires that have been specifically developed for providers’ perceptions on appropriateness, feasibility, and harm of the program, as well as SUS items. Hospital managers will be asked to answer the iOSDMH questionnaires for managers that have been developed to evaluate the perceptions of managers, as well as SUS items.

#### Sample size calculation

As the study has two co-primary outcomes, we calculated each sample size needed to improve the depressive symptoms of mothers and to prevent abusive behaviours toward children based on the effect size from a previous study.

The study reported the effect size of the internet-based behavioural activation for postnatal depression as d = 0.55 [32]. With a significance level of 0.05, the statistical power of 80%, and a follow-up rate of 85%, the sample size needed to detect efficacy for postnatal depression in the high EPDS group is 128 participants (64 participants for each arm). (Sample size calculation was carried out using the G*Power 3.1.9.2.)

No previous study examined the effect of iBA for preventing child abuse, so we used the effect size d = 0.56 of cognitive behavioural therapy for anger from a randomized controlled trial [64]. We estimated the effect size of the iBA for psychological aggression as d = 0.50 for the high EPDS group based on the previous study [64], and d = 0.40 for the low EPDS group. With a significance level of 0.05, the statistical power of 80%, and a follow-up rate of 80%, the required sample size is 150 participants for the high EPDS group (75 participants per arm) and 240 participants for the low EPDS group (120 participants per arm).

Finally, we expected the sample size needed to detect the change in both depressive symptoms and abusive behaviours would be 150 participants for the high EPDS group and 240 participants for the lower EPDS group.

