### Study design

The study is a non-blinded, parallel group, stratified randomized controlled trial. Based on the most recent score of the Edinburgh Postnatal Depression Scale (EPDS) at recruitment, participants will be stratified to either low EPDS group (EPDS 0–8 points) or high EPDS group (EPDS ≥9 points) after completing the baseline survey. The threshold of 8/9 points was determined fit according to the previous validation studies conducted in Japan [50, 51].

The allocation ratio of the intervention group to the control group is set as 1:1. Participants will be asked to answer the online follow-up surveys at 12 and 24 weeks after the initiation of the program. The protocol of the study was registered at UMIN Clinical Trial Registry (UMIN-CTR: ID UMIN 000036864). As of February 2021, we are in the process of recruiting participants. The study protocol follows the Standard Protocol Items for Randomized Trials (SPIRIT) guideline checklists.

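### The CTS-1 stratum sizes of 150 and 240 do not follow from the stated 80% follow-up; the same inputs give 160 and 250 (minor; the all-mothers CTS-1 test is not underpowered by it)

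*Protocol article*

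**What the plan says.** The section Sample size calculation of the protocol article sizes each co-primary outcome separately.

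- **EPDS, high-EPDS group:** d = 0.55, with "the statistical power of 80%, and a follow-up rate of 85%, the sample size needed to detect efficacy" given as 128 (64 per arm).
- **CTS-1, both groups:** it assumes an "effect size of the iBA for psychological aggression as d = 0.50 for the high EPDS group" and "d = 0.40 for the low EPDS group". At 80% power it then states: "a follow-up rate of 80%, the required sample size is 150 participants for the high EPDS group (75 participants per arm) and 240 participants" (the last figure being the low group, 120 per arm).
- **Adopted sizes:** the number needed for both outcomes "would be 150 participants for the high EPDS group and 240 participants for the lower EPDS group", which makes the 390 in the Abstract.

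Under Study design, "The allocation ratio of the intervention group to the control group is set as 1:1". The calculation was done in G*Power. Whether the test is one- or two-sided is not stated.

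**The concern.** Every input to the CTS-1 calculation is printed, so a reader can recompute it, and the printed result does not come back. The numbers fix the total enrolment and concern a co-primary outcome. If 150 and 240 are too small for the stated inputs, the claim of 80% power within each stratum is inaccurate.

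The section also plans for two retention rates, 85% for EPDS and 80% for CTS-1. The assessment schedule (Table 2) collects both scales at the same 24-week follow-up, so one group of high-EPDS mothers is being planned at two rates, with no reason given.

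**Working it through.** **Inputs.** From Sample size calculation: alpha 0.05, power 80%, follow-up 80%, d = 0.50 (high) and 0.40 (low). From Study design: 1:1 allocation. Two-sided testing is assumed.

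**1. Completers per arm.** The normal approximation is n = 2(1.960 + 0.842)²/d² = 15.70/d².

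- d = 0.50: 15.70/0.25 = 62.8
- d = 0.40: 15.70/0.16 = 98.1

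The exact t-test, as in G*Power, gives 63.8 and 99.1, so 64 and 100 per arm.

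**2. Inflation for 80% follow-up (divide by 0.80).**

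| Stratum | Completers per arm | Enrolled per arm | Enrolled in stratum | Stated | Shortfall |
|---|---|---|---|---|---|
| High | 64 | 64/0.80 = 80 | 160 | 150 | 10 (6%) |
| Low | 100 | 100/0.80 = 125 | 250 | 240 | 10 (4%) |
| Total | | | 410 | 390 | 20 |

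**3. Attempts to reproduce 150 and 240.**

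- Normal approximation, 80% follow-up: 158 and 248 (246 in the low group if n is not rounded before inflation).
- One-sided test, 80% follow-up: 124 to 128 and 194 to 196.
- 85% follow-up: about 150 to 152 in the high group, but about 234 to 236 in the low group.
- Multiplying by 1.20 instead of dividing by 0.80: 200 × 1.20 = 240 exactly, but 128 × 1.20 = 153.6 (154 when rounded per arm), not 150.

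With correct inflation, 150 corresponds to 128/150 = 85.3% follow-up and 240 to 200/240 = 83.3%. No single rate yields both.

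**4. Power with the stated sizes at 80% follow-up.** The noncentrality is d√(m/2), with m completers per arm.

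- High: m = 75 × 0.80 = 60; 0.50 × √30 = 2.74; power 77.5% (78.2% by normal approximation).
- Low: m = 120 × 0.80 = 96; 0.40 × √48 = 2.77; power 78.7% (79.1% by normal approximation).

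The follow-up needed for 80% power is 63.8/75 = 85% (high) and 99.1/120 = 83% (low).

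**5. The all-mothers test (H2).** m = 390/2 × 0.80 = 156 per arm.

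- d = 0.40: 0.40 × √78 = 3.53; power 94%.
- Weighted d = (0.50 × 150 + 0.40 × 240)/390 = 171/390 = 0.44; power 97%.

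**6. EPDS, high group, d = 0.55.** The t-test needs 52.9, so 53 completers per arm; 53/0.85 = 62.4, so 63 per arm and 126 in all. The stated 128 is therefore adequate. In the 150 women adopted, 80% follow-up leaves 60 per arm and gives 84.8% power.

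**7. Baseline adjustment.** ANCOVA reduces the required n by the factor 1 − r², where r is the correlation of baseline with 24-week score.

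- High: 1 − r² = 60/64, so r = 0.25.
- Low: 1 − r² = 96/100, so r = 0.20.

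These are the correlations at which 80% is restored. The protocol gives no value of r.

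**The case against.** The strongest reply is that nothing confirmatory depends on the slip. H2 is stated for all mothers, Statistical methods describes one CTS-1 comparison between the arms, and initial EPDS appears as a subgroup factor. On that reading the CTS-1 test has well over 80% power under the stated effects. This stands. A reader might infer from the recomputation that the trial lacks its stated power on a co-primary outcome; the documents do not support that.

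Second, 77.5% and 78.7% are for an unadjusted t-test, while the planned analysis is ANCOVA on the baseline score, and a modest correlation would close the gap. This stands as a reason not to say that 80% is out of reach in either stratum. It does not repair the printed calculation, which names no correlation and takes no credit for one.

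Third, shortfalls of 2.5 and 1.3 percentage points are small beside the uncertainty in d, which the protocol takes from a trial of cognitive behavioural therapy for anger because no direct evidence existed. This also stands and bears on severity.

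Fourth, the two retention rates do little harm, because 128 is not the size adopted and EPDS keeps about 85% power at the lower rate. That is correct, but the two rates still cannot both describe one survey.

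**Conclusion.** Wrong as written, but minor. The sizes called required for CTS-1 are 10 women short in each stratum against the section's own inputs. At 80% follow-up the unadjusted within-stratum power is about 77.5% and 78.7%, not 80%. This rests on a two-sided test, which the protocol does not state; one-sided testing does not recover the printed figures either.

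The source of the slip cannot be determined. It is tempting to blame multiplication by 1.20, but that fits only the 240 exactly, while 85% follow-up fits only the 150.

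Power for H2 is about 94% to 97%. That range assumes the stated effects, a common standard deviation across strata and 80% follow-up. It is the power of the CTS-1 test itself, not the chance of passing both steps of the fixed sequence. At a pooled d of 0.30, below anything the section assumes, it would be about 75%.

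**What to change.** Keep 150 and 240, and use one follow-up rate for both outcomes. At 80%, state:

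- unadjusted within-stratum CTS-1 power of about 77.5% (high) and 78.7% (low), labelled as such;
- pooled CTS-1 power for H2 of about 94% to 97%;
- EPDS power of about 85% in the 150 high-EPDS mothers at d = 0.55.

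If 85% is chosen instead, with a reason, the CTS-1 figures are about 80.0% and 81.1%, and EPDS about 86.9%.

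Alternatively, restate the calculation for the planned ANCOVA with a named baseline correlation, marked as an assumption; about 0.25 (high) and 0.20 (low) restore 80% at the same sizes and 80% follow-up. In either case, say whether the test is two-sided.

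The cost is a wording change. No participants are added and neither design nor analysis changes. If 80% follow-up is kept without baseline adjustment, the stated per-stratum power becomes slightly less favourable.

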### Statistical methods

#### Clinical efficacy

For primary outcomes, an analysis of covariance (ANCOVA) will be conducted to compare the mean differences of co-primary outcomes at 24 weeks follow-up between the intervention and TAU groups after adjusting baseline scores. The study sets two co-primary outcomes, including the EPDS scores at 24 weeks after the initiation of the program and psychological aggression toward children measured by the CTS-1 scores at the 24 weeks follow-up survey. The order of statistical testing is as follows: (1) the EPDS scores at 24 weeks follow-up; (2) CTS-1 scores at 24 weeks follow-up. If we find statistical significance for the EPDS scores at the predefined 0.05 level, then we will conduct statistical testing for the CTS-1 scores. If we do not find statistical significance for the EPDS scores, we will conduct the ANCOVA for the CTS-1 score as a complementary analysis. Given the fixed-sequence testing procedure, the study will not adjust for the multiplicity of each statistical test.

For secondary outcomes, the ANCOVA will be conducted to compare secondary outcome measures (Table 2) between the TAU and intervention groups after adjusting baseline scores. Statistical analyses will be performed using the SAS version 9.4 (SAS Institute, Cary, North Carolina, USA).

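### The stand-alone 80% power per outcome does not support the by-group claim that the sample is enough to detect both outcomes under the EPDS-first testing sequence

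*Protocol article*

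**What the plan says.** Sample size calculation treats the two outcomes one at a time: "we calculated each sample size needed to improve the depressive symptoms of mothers and to prevent abusive behaviours toward children". For EPDS in the high-EPDS group it takes d = 0.55, 80% power and 85% follow-up and arrives at 128 women. For CTS-1 it takes d = 0.50 (high group) and 0.40 (low group), 80% power and 80% follow-up, and arrives at 150 and 240. The section closes by adopting the larger number in each group as sufficient for both outcomes: "we expected the sample size needed to detect the change in both depressive symptoms and abusive behaviours would be 150 participants for the high EPDS". For the low group the number is 240.

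Clinical efficacy sets an order, EPDS first: "If we find statistical significance for the EPDS scores at the predefined 0.05 level, then we will conduct statistical testing for the CTS-1 scores". The alternative branch reads: "If we do not find statistical significance for the EPDS scores, we will conduct the ANCOVA for the CTS-1 score as a complementary analysis". On multiplicity it adds: "Given the fixed-sequence testing procedure, the study will not adjust for the multiplicity of each statistical test".

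Two other places matter. Objectives puts H1 (EPDS) in mothers scoring 9 or more and H2 (CTS-1) in all mothers, without splitting H2 by EPDS group. Co-primary outcomes explains the pairing: "We have set two co-primary outcomes, as both maternal and child outcomes were considered equally important".

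**The concern.** The sample size section describes two free-standing tests. The analysis section describes a gate. Behind a gate, the confirmatory power of the second test is the probability that both tests are significant, so it cannot exceed the power of the first. Choosing the larger of two single-test sample sizes protects each test alone but does not fix that joint probability. The sentence about detecting both outcomes therefore does not follow from the calculation above it.

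At stake is what the trial can be expected to show about the child outcome. A CTS-1 result becomes complementary whenever the EPDS test misses, and the EPDS test is run in the smaller population. A reader who takes 80% as the chance of a confirmatory CTS-1 finding in either EPDS group is misled. The document also leaves two populations in play for CTS-1: all mothers in Objectives, and separate EPDS groups in Sample size calculation. The size of the problem depends on which is meant.

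**Working it through.** **Inputs from the protocol.** EPDS d = 0.55 (high group). CTS-1 d = 0.50 (high) and 0.40 (low). Significance level 0.05 for each test, 1:1 allocation, 150 + 240 = 390 women, and 80% follow-up as used for CTS-1.

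**Assumptions not in the protocol.** Two-sided tests. Correlation r between the two test statistics in the same women of 0 to 0.7. No gain from baseline adjustment. The same 80% follow-up for EPDS at the final sample size.

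**Method.** Single-test power comes from the two-sample t-test with noncentrality d × √(n/2), where n is completers per arm. Power for both is the bivariate normal probability that both tests reject, given their single-test powers and correlation. At r = 0 this is the product of the two powers.

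**Step 1: the plan's own figures.**
- EPDS: 53 completers per arm give 80%; 53 / 0.85 = 62.4, so 63 per arm, 126 in total, against 128 stated. This reproduces closely, and two-sided testing is what fits (one-sided gives 100).
- CTS-1, high group: 64 / 0.80 = 80 per arm, 160 in total, against 150 stated.
- CTS-1, low group: 100 / 0.80 = 125 per arm, 250 in total, against 240 stated.

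The two CTS-1 figures fall short because of the allowance for dropout. That is a separate matter, and Step 3 removes its effect.

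**Step 2: both outcomes in the 150 high-EPDS women.** Completers per arm: 75 × 0.80 = 60. EPDS alone has 84.8% and CTS-1 alone 77.5%.

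| Assumed r | Power for both |
|---|---|
| 0 | 0.848 × 0.775 = 65.7% |
| 0.3 | 68.1% |
| 0.5 | 70.0% |
| 0.7 | 72.4% |

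**Step 3: the same with the dropout shortfall removed.** With 64 completers per arm, CTS-1 alone has 80.1% and EPDS 87.0%. Power for both is 69.7% (r = 0), 71.8% (0.3), 73.5% (0.5) and 75.5% (0.7). The gap to 80% is therefore not just the dropout arithmetic.

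**Step 4: CTS-1 in the low group behind the gate.** Completers per arm: 120 × 0.80 = 96, giving 78.7% alone. The EPDS test uses different women, so the results are independent: 0.848 × 0.787 = 66.8%.

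**Step 5: the hypotheses as Objectives states them.** EPDS in the high group, then CTS-1 in all 390.
- Weighted d = (150 × 0.50 + 240 × 0.40) / 390 = 171 / 390 = 0.438.
- Completers per arm: 195 × 0.80 = 156.
- CTS-1 alone: 97.1%.
- The tests share only the high-EPDS women, so the correlation of the statistics is r × √(150/390) = 0.62r.
- Power for both: 82.4% (r = 0), 82.7% (0.3), 83.0% (0.5) and 83.3% (0.7). If r is applied without scaling for the overlap, the top of the range is 84.2%.

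The limit here is the EPDS gate at 84.8%, not the CTS-1 test.

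**The case against.** A reader might infer that the trial as a whole has only 66-72% power for its two primary outcomes. The documents do not support that. Objectives places H2 in all mothers and Clinical efficacy does not confine the CTS-1 test to one EPDS group, so the planned sequence has about 82-83% on the plan's own inputs. This objection stands in full, and it is why the point is limited to the by-group statement.

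It can also be said that the protocol never claims 80% joint power in so many words: it attaches 80% to each outcome, and a fixed sequence does not need both tests to succeed. That is correct, and the EPDS claim keeps its own power of about 85%. But the closing sentence speaks of both outcomes, group by group, and nothing in the section supports it in that form.

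Third, the planned analysis is ANCOVA. If the quoted effect sizes are on the unadjusted scale, baseline adjustment helps: joint power in the high group rises to about 71-77% at an assumed baseline correlation of 0.3 and to about 82-85% at 0.5. The protocol gives no baseline correlation and claims no such gain, so the unadjusted figures are conditional rather than certain.

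Last, one might infer that the fixed sequence is itself an error, given that the outcomes are called equally important. It is not. It controls the family-wise error validly, and the protocol states both the order and its consequence openly.

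**Conclusion.** The point holds in a limited form. The 80% is a per-outcome, stand-alone figure, and the statement that 150 and 240 women suffice for both outcomes does not follow under the written sequence.

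- **By EPDS group:** about 66-72% for both in the high group (69.7-75.5% once the dropout shortfall is removed), and about 67% for gated CTS-1 in the low group.
- **For H1 then H2 in all mothers:** about 82-83%, so no shortfall below 80% on the plan's assumptions.

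All figures rest on the plan's effect sizes, two-sided testing, 80% follow-up, the assumed correlations and no ANCOVA gain. The 82-83% also depends on the EPDS effect of 0.55, because the gate sets the ceiling. The type I error rate is unaffected. What needs correcting is the power statement, together with the unresolved population for the confirmatory CTS-1 test.

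**What to change.** In Sample size calculation:

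1. Say that 80% applies to each outcome tested alone.
2. Replace the closing sentence about both outcomes with the power under the written sequence, and give its assumptions: correlation, follow-up rate and no gain from ANCOVA.
3. Reconcile this section with Objectives on whether the confirmatory CTS-1 test is in all mothers or by EPDS group, and report the power for the version chosen.

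The sample size need not change. The only cost is a less favourable by-group figure.

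Replacing the fixed sequence with Holm is an optional design choice, not a correction, and would be a design amendment to a registered trial that is already recruiting. With CTS-1 tested in all mothers, Holm would raise confirmatory CTS-1 power from 82.4-83.3% to about 96-97%, a gain of about 13-14 points. The cost to EPDS depends on the true CTS-1 effect. It is under 1 point if the assumed effect holds, but about 8 points (from about 85% to about 77%) if CTS-1 has no effect, since EPDS is then nearly always tested at 0.025. The protocol says no earlier study has examined this intervention for preventing child abuse and borrows its CTS-1 effect from a trial of therapy for anger, so that second case cannot be set aside.
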